### Ethical Considerations

For phase 1, approval was granted by the research committee of the RCGP RSC. The study did not meet the requirements for a formal ethics board review as per the NHS Health Research Authority’s research decision tool [24]. The study was conducted in line with the REporting of studies Conducted using Observational Routinely-collected Data (RECORD) guidelines [25]. For phase 2, personal data were not collected from the study participants. Participants were informed that their verbal responses and screen activities would be recorded. All participants received oral and written information about the study.

### Dissemination

The protocol and data produced from this work will be submitted for publication in a peer-reviewed journal covering the domains of cardiology, epidemiology, and primary care. Additional opportunities include presentation at seminars, conferences, and meetings.

## Results

We received funding for both phases in January 2019 and received approval from RCGP RSC research committee in March 2019. We completed data extraction for phase 1 in May 2019 and completed analysis in December 2019. We completed building the AF dashboard in May 2019. We started recruiting participants for phase 1 in May 2019 and concluded data collection in July 2019. We completed data analysis for phase 2 to in October 2019. As of October 2020, the publications reporting the results are under review.

## Discussion

The RCGP RSC sentinel network has a large dataset, which is representative of information regarding primary care practices on management of AF. The quantitative analysis will report on the current trends of anticoagulant prescribing using a real-world data set in the United Kingdom and the overall population effect of the use of DOAC use.

Missing/incomplete data could be a potential issue in this analysis. We intend to reduce the effect of this issue by incorporating an ontological approach, considering practice level variations in the anticoagulation prescribing.

The qualitative analysis of the dashboard will indicate the priority of sections that require an improved user experience. We intend to enhance the dashboard using the outcomes of the usability study and deploy to general practices in the RCGP RSC sentinel network.

As the incidence of AF has increased over the years, there is a greater focus on early recognition of AF in general practice to allow for early intervention. This study will give insights into the current trends in management of AF using real-world data from the Oxford RCGP RSC database. We anticipate that the outcomes of this study will be used to guide the development and implementation of an audit-based intervention tool for use in primary care settings to assist practitioners in identifying and managing AF.

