**Objective:**

The primary aim of this study is to investigate if patients are managed in general practice according to current national guidelines. In addition, the study will evaluate the impact of direct oral anticoagulant use with respect to AF complications in a real-world dataset. The secondary aims of the study are to develop a dashboard that will allow monitoring the management of AF in general practice and evaluate the usability of the dashboard.

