**Methods:**

The study was conducted in 2 phases. The initial phase was a quantitative analysis of routinely collected primary care data from the Oxford Royal College of General Practitioners Research and Surveillance Center (RCGP RSC) sentinel network database. AF cases from 2009 to 2019 were identified. The study investigated the impact of the use of anticoagulants on complications of AF over this time period. We used this dataset to examine how AF was managed in primary care during the last decade. The second phase involved development of an online dashboard for monitoring management of AF in general practice. We conducted a usability evaluation for the dashboard to identify usability issues and performed enhancements to improve usability.

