## Introduction

Atrial fibrillation (AF) is one of the commonest arrhythmias observed in clinical practice [1]. Globally, the incidence of AF is rising. The thromboembolic complications of AF can lead to significant disabling consequences for patients, including transient ischemic attack, stroke, and pulmonary embolism. Early recognition of AF in general practice can lead to early intervention with managing the risks of these complications.

Current guidelines on the management of AF by the National Institute for Health and Care Excellence (NICE) advise identifying and managing the underlying causes of AF, treating the arrhythmia, and assessing and managing the risk of stroke in these patients [2]. Risk of stroke is determined by the CHA_2_DS_2_-VASc (Congestive heart failure, Hypertension, Age, Diabetes, previous Stroke/transient ischemic attack–VAScular disease) assessment tool [3], which guides the practitioner on commencing anticoagulation treatment to manage this risk. The risk of starting a patient on anticoagulation is assessed using the HAS-BLED (Hypertension, Abnormal renal/liver function, Stroke, Bleeding history or predisposition, Labile international normalized ratio, Elderly, Drugs/alcohol concomitantly) score, assessing for major bleeding risks [4].

Anticoagulation therapy aims to reduce the risk of thromboembolic events. This has been achieved using warfarin (a vitamin K antagonist) for many years. The introduction of direct oral anticoagulants (DOACs) such as apixaban and rivaroxaban to clinical practice has changed how AF is managed in clinical practice [5]. In comparison to warfarin, DOACs are observed to have similar or better mortality and vascular outcomes [6]. They have the added benefit of requiring no monitoring, as opposed to warfarin use [7]. Though studies have highlighted that increased number of patients in clinical practice are receiving treatment for AF [8], whether they are managed according to national or local guidelines is unclear. Better understanding of current management trends of AF in population will guide practitioners on how best to employ interventions in clinical practice to increase awareness of AF and early recognition.

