The aim of this study is to understand the disease and prescribing trends related to AF in general practice. We also aim to develop a system to monitor practice-level indicators for AF of the same trends and evaluate the usability of this system. The primary objective of this study is to investigate if people with newly diagnosed AF treated with DOACs versus warfarin have any difference in stroke or all-cause mortality in long-term follow-up. The secondary objectives of this study are to develop an AF dashboard as an intervention method at a practice level and to evaluate the usability of the AF dashboard.

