#### Exposures and Outcomes

We considered the exposure as continuous anticoagulant prescription for the first time after receiving an AF diagnosis. Although almost all anticoagulant prescriptions in the United Kingdom are issued from primary care if an anticoagulant is started in a hospital, we measured exposure from the first general practice prescription. We excluded patients who had an interval of greater than 90 days between anticoagulant prescriptions.

Outcomes are first records of stroke and all-cause mortality based on previously published Read codes [16,17] Stroke was included regardless of etiology, an approach used in other studies [18,19]. Study participants were followed for stroke and all-cause mortality till the end of the study period.

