### Statistical Analysis

Analysis of data extracted from general practice CMR was carried out using the statistical software R. We studied the influence of the anticoagulation regimen by evaluating the cause-specific hazard ratio and the subdistribution hazard ratios of both events. Additionally, we estimated cumulative incidence for both events by direct regression, utilizing the inverse of the probability of censoring weights method [15] with time-varying effects [20]. We will report and interpret both cause-specific and subdistribution analyses. The cause-specific hazard ratio is often interpreted as estimating etiological association, estimating associations between covariates, and the rate at which events occur in those participants who are event-free. The cause‐specific hazard ratio can be interpreted as a rate ratio. Whenever the proportional hazards assumption was violated, we interpreted all hazard ratios as time-averaged effects.

We will determine the (adjusted) incidence and prevalence of AF for each year along with the proportion of incident and prevalent cases treated with nothing, antiplatelet medications only (eg, aspirin), and anticoagulant therapy (warfarin/types of DOACs). We will also determine the number of strokes, transient ischemic attacks, deaths, and bleeds in the incident and prevalent cases per year.

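### The article promises the impact of anticoagulant use and a population effect of DOACs, but its only outcome contrast is DOAC versus warfarin among continuously treated patients

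*Protocol article*

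**What the plan says.** Three places in the protocol article set out what phase 1 will show about anticoagulants.

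- Abstract, Methods: "The study investigated the impact of the use of anticoagulants on complications of AF over this time period".
- Abstract, Objective: "the study will evaluate the impact of direct oral anticoagulant use with respect to AF complications in a real-world dataset".
- Discussion: the quantitative analysis will report prescribing trends and "the overall population effect of the use of DOAC use".

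The operative parts are narrower.

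- The end of the Introduction gives the primary objective as whether people with "newly diagnosed AF treated with DOACs versus warfarin have any difference in stroke or all-cause mortality in long-term follow-up".
- Exposures and Outcomes: "We considered the exposure as continuous anticoagulant prescription for the first time after receiving an AF diagnosis". Exposure is measured from the first general practice prescription, and patients with more than 90 days between prescriptions are excluded.
- Case Ascertainment also excludes patients with a previous stroke and those not on the recommended DOAC dose.
- Statistical Analysis: "We studied the influence of the anticoagulation regimen by evaluating the cause-specific hazard ratio and the subdistribution hazard ratios of both events".

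The second paragraph of Statistical Analysis adds a descriptive part. It covers yearly incidence and prevalence of AF, the share of cases on no treatment, on antiplatelet drugs alone or on an anticoagulant (warfarin or DOAC type), and then: "We will also determine the number of strokes, transient ischemic attacks, deaths, and bleeds in the incident and prevalent cases per year".

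**The concern.** The effect of using anticoagulants is a contrast between use and non-use. An overall population effect of DOACs concerns all AF patients, including those who take nothing, those on antiplatelet drugs alone, and those whose chance of being treated changed when DOACs arrived. A hazard ratio for DOAC versus warfarin among continuous users addresses neither. It says which drug went with fewer events among people who were taking one of them.

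What is at stake is the conclusion drawn. A ratio near 1 could be reported as little population effect of DOACs, although the analysis would not have examined whether treatment reached more people. A favourable ratio could be extended to AF patients who were never in the comparison. The Discussion expects the results to guide an audit tool for identifying and managing AF in primary care, where the position of untreated patients matters directly.

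**Working it through.** The plan gives no figure to reproduce on this point: phase 1 has no sample size, event rate, treatment share or target effect. The check is to set each promise against what is specified.

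1. **Impact of anticoagulant use (Abstract, Methods).** This needs a group without anticoagulants in the outcome comparison. Exposure is a first continuous anticoagulant prescription and is measured from that prescription. An untreated patient has no such date, and no other starting point is given. The objective names warfarin as the comparator. Result: not estimated.

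2. **Impact of DOAC use (Abstract, Objective).** No comparator is named there. Read as relative to warfarin, it is answered by the primary objective. Result: no mismatch on that reading.

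3. **Overall population effect of DOAC use (Discussion).** This depends on untreated patients, on any change in uptake of treatment, and on patients excluded from the comparison (previous stroke, not on the recommended DOAC dose, prescription gap over 90 days). None of them is in the hazard model. Result: not estimated.

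4. **Can the descriptive part supply it?** Untreated patients do appear there, in the treatment shares and among the cases whose events are counted. But the event sentence classifies cases only as incident or prevalent, by year. It gives numbers, not rates, so a rise in AF cases would raise the counts by itself. No contrast or model links events to treatment. Result: a time trend that cannot be attributed to DOACs.

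**Illustration of how far two different questions can diverge (all inputs assumed).** Let h be the DOAC-versus-warfarin stroke ratio, RW the warfarin-versus-untreated ratio, and s the share of DOAC users who would otherwise have had no anticoagulant. Compared with what DOAC users would otherwise have received, the ratio is

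h × RW / [(1 − s) × RW + s].

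With h = 0.9:

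| RW | s | Calculation | Ratio |
|---|---|---|---|
| any | 0 | h | 0.90 |
| 0.5 | 0.10 | 0.45 / 0.55 | 0.82 |
| 0.5 | 0.20 | 0.45 / 0.60 | 0.75 |
| 0.5 | 0.30 | 0.45 / 0.65 | 0.69 |
| 0.4 | 0.20 | 0.36 / 0.52 | 0.69 |
| 0.7 | 0.20 | 0.63 / 0.76 | 0.83 |

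The 0.90 is the correct answer to the stated objective; the other values answer another question. The gap is a difference between estimands, not a bias in the planned analysis. The formula also covers DOAC users only, not the whole AF population.

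**The case against.** The best defence is that the operative chain is consistent. The objective names DOAC versus warfarin, the exposure and outcomes match it, and the model estimates it. Comparing two active drugs is a defensible way to limit confounding by indication, which an untreated comparator would bring in. This stands in full. A reader might infer that the primary comparison is biased or needs an untreated arm; the article does not support that.

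Second, the Discussion sentence pairs the population effect with prescribing trends, so it may refer to the yearly descriptive tables, which include untreated patients. This stands in part. It shows that those patients are not absent from the reporting, but a trend is not an effect, and the sentence says that the analysis will report one.

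Third, a split of events by treatment may sit in a fuller plan that is not shown. That is possible, and it is why the main point is the claim rather than the table layout. Even with such a split, crude treated-versus-untreated figures would not identify a population effect.

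A further tempting step is to argue from the Introduction that some DOAC users must otherwise have been untreated. The text there reports an "increased number of patients in clinical practice are receiving treatment for AF". That is a number, not a share; it does not specify anticoagulants and does not credit DOACs. The article also says that AF incidence is rising, which alone would raise the number. The inference is plausible but not established.

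Finally, the article reaches no conclusion about a population effect and sets no decision rule for one, so misreading is a risk and not a demonstrated harm.

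**Conclusion.** The mismatch holds, and it concerns the claims, not the primary comparison. DOAC versus warfarin for stroke and all-cause mortality is a sound objective with a matching analysis. The wording in the Abstract's Methods and in the Discussion goes beyond it, and neither the hazard ratios nor the yearly counts support the wider claims.

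No size can be given from the article. The logical point needs no assumed figure: it follows from the stated comparator, exposure definition and exclusions. It matters because it changes what the study may conclude, and it should be corrected. It is no reason to change the primary analysis.

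**What to change.** 1. **Wording in the Abstract's Methods and the Discussion.** State the estimated effect as DOAC versus warfarin in eligible, newly and continuously treated AF patients without previous stroke, together with descriptive time trends. Say explicitly that neither a population effect of DOAC introduction nor an effect of anticoagulation versus none will be concluded. Leave the primary objective in the Introduction as it is. The article says that the analysis was complete in December 2019 and that the results papers were under review in October 2020, so the same limits should be carried into those papers.

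2. **Second paragraph of Statistical Analysis.** Replace the raw yearly counts with stroke, death and bleed rates per person-year, by calendar year and by the treatment categories already listed there: none, antiplatelet only, warfarin, DOAC. Assign person-time to the treatment current at that time, so that time before a first prescription is not credited to the drug. Standardise for age, sex and comorbidity, and state whether the exclusions used for the hazard model also apply. Label the tables as descriptive because of confounding by indication; they add context but do not themselves identify a population effect.

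The first change costs a narrower headline claim. The second costs one extra set of tables, which should need no new data collection, since the article already plans both the treatment shares and the event counts.

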## Appendix

Multimedia Appendix 1 Supplementary file with Table 1 and Table 2 described in the study design of phase 2.

## Abbreviations

AF: atrial fibrillation
CHA2DS2-VASc: Congestive heart failure, Hypertension, Age, Diabetes, previous Stroke/transient ischemic attack–VAScular disease
CMR: computerized medical records
DOAC: direct oral anticoagulant
HAS-BLED: Hypertension, Abnormal renal/liver function, Stroke, Bleeding history or predisposition, Labile international normalized ratio, Elderly, Drugs/alcohol concomitantly
IMD: Index of Multiple Deprivation
NICE: National Institute for Health and Care Excellence
P4P: pay-for-performance
RCGP RSC: Royal College of General Practitioners Research and Surveillance Center
RECORD: REporting of studies Conducted using Observational Routinely-collected Data
